## Abstract

**Background:**

Sexual and gender minority (SGM) persons experience substantial mental health disparities throughout the life course, including increased vulnerability to depression and suicide. Few existing studies, however, have explored how pervasive experiences of SGM-related stigma, discrimination, and trauma (i.e., minority stress) contribute to adverse mental health outcomes among diverse sub-populations of SGM adults living in rural areas of the United States. This paper describes the protocol for a prospective cohort study, “Rural Exploration and Approaches for LGBTQ + Mental Health (REALM),” that will explore minority stress in relation to mental health conditions and suicidal behaviors among rural SGM adults.

**Methods:**

Online processes will be used to recruit and enroll a diverse sample of up to 2,500 SGM adults aged 18 + living in rural counties and small metropolitan areas in the United States to complete an online baseline survey. This will include: up to 1,000 cisgender sexual minority persons (up to *n* = 500 each cisgender women and cisgender men); and up to 1,500 gender minority persons (up to *n* = 500 persons who were assigned male at birth and identify as a woman, female, and/or transfeminine; up to *n* = 500 persons who were assigned female at birth and identify as a man, male, and/or transmasculine; and up to *n* = 500 persons who identify as some other gender, including non-binary, gender non-conforming, and/or agender regardless of sex assigned at birth). All enrolled participants will subsequently be followed over a 12-month period, with repeated surveys at three-month intervals. Included survey measures will focus on sociodemographic information, mental health, substance use, suicidal behaviors, minority stressors, psychological processes, and other related risk and protective factors.

**Discussion:**

This study presents a critical opportunity to better understand how minority stress contributes to adverse mental health outcomes among populations that remain underrepresented in research and programs in 2024. Results will be used to create more targeted, acceptable, and impactful intervention content and strategies that mitigate stigma, promote mental health, and prevent suicidal behaviors among rural SGM adults.

## Background

Sexual and gender minority (SGM) persons – including but not limited to those who identify as lesbian, gay, bisexual, transgender, and queer (LGBTQ+) – experience a high burden of mental disorders, substance use disorders, and suicidal behaviors [1–3]. Further, a large body of research shows substantial disparities in mental health across the life course between SGM persons and their heterosexual, cisgender peers [1–9]. For instance, the 2022 National Survey on Drug Use and Health noted that in the past year, nearly half of sexual minority adults had a mental disorder compared to one fifth of heterosexual adults, and around one in five had a substance use disorder compared to less than one in ten heterosexual adults [5]. Both mental disorders and substance use disorders have been found to be associated with suicidal behaviors among sexual minority persons [10, 11], and one large comparative study of suicide decedents in the United States (US) suggests that these associations may be stronger among sexual minority persons compared to their heterosexual peers [10]. Similar patterns have been documented among gender minority persons [2, 3, 7, 9]. For example, a recent study included a nationally representative sample of US adults and found that when compared to their cisgender peers, transgender adults reported significantly higher odds of serious psychological distress (aOR = 3.1), recent suicidal ideation (aOR = 5.1), lifetime suicidal ideation (aOR = 6.7), and lifetime suicide attempts (aOR = 4.4) [9].

While the suboptimal mental health and suicidal behaviors experienced by SGM persons are well-documented, the upstream determinants of these disparities have not been extensively studied [12]. The Minority Stress Model suggests that societal marginalization of SGM persons results in specific distal stressors (i.e., external stressors such as discrimination, violence, and harassment) and proximal stressors (i.e., internal stressors such as internalized homophobia or transphobia, anticipated rejection, and identity concealment) which may be responsible for driving the relatively higher prevalence of poor mental health outcomes compared to the general population [13–15]. These stressors are reflective of stigma, a complex social process in which an individual is labeled based on a specific characteristic, linked to a negative stereotype, and set apart from others based on perceived differences, resulting in experiences of discrimination, marginalization, and devaluation [16]. Studies informed by this theory have generated broad evidence for the role of minority stress processes in creating and sustaining disparities in mental health for SGM persons [17–19]. For instance, a systematic review of 30 studies found that discrimination was consistently associated with both greater suicidal ideation and attempts for transgender adults, although the cross-sectional design of most studies precluded causal interpretations [20].

Combining minority stress models with suicide theory can help elucidate modifiable mechanisms through which stigma produces mental health disparities among SGM persons [21, 22]. A multitude of theories for understanding suicide-related outcomes exist, including several “ideation-to-action” theories that conceptualize suicidal ideation and attempts as having distinct underlying processes [23]. The Interpersonal-Psychological Theory of Suicidal Behavior (IPTS), for example, posits that thwarted belongingness and perceived burdensomeness lead to suicidal ideation, while the capability to act precipitates suicide attempts [24]. Importantly, it has been argued that painful and traumatic experiences may desensitize individuals to the fear of pain and death that serves as a deterrent to attempted suicide [24]. This may be particularly relevant for SGM persons given a higher documented prevalence of interpersonal traumas across the life course, including abuse during childhood, bullying victimization, and sexual assault [25–28]. Indeed, IPTS and related theories have increasingly been integrated to guide mental health research among SGM persons. For instance, among gender minority participants in the US Trans Health Survey, Testa et al. found that while distal stressors acted through proximal stressors in relation to suicidal ideation, thwarted belongingness and perceived burdensomeness mediated this relationship [29]. This has led other SGM researchers to conclude that minority stress models alone are insufficient for characterizing the processes that shape SGM suicide disparities [21].

Despite progress, significant gaps remain in understanding mental health disparities among SGM populations; chief among them is the lack of data on SGM persons living in rural areas. This is a critical limitation, as evidence drawn from the general population suggests that suicide rates are higher in rural compared to urban settings, potentially due to increased social isolation, greater access to lethal means, heightened stigma around mental health, and poor access to mental health services [30]. Importantly, the limited studies that do focus on rural SGM populations indicate that mental health disparities may be intensified in these areas: both when compared to rural cisgender, heterosexual adults [31, 32] and when compared to urban SGM populations [33–37]. There are several potential explanations for these patterns. Rural SGM populations may contend with substantial stigma and discrimination, limited social capital, and lower healthcare access and utilization [38–40]. There may also be important differences in mental health and suicide risk factors between SGM and non-SGM persons living in rural areas. For instance, sexual orientation change efforts (e.g., conversation therapy), 80% of which are implemented by religious leaders, have been associated with increased suicidal ideation and behaviors among sexual minority persons [41], and both religiosity and religious services attendance have been found to be higher in rural vs. urban areas [42–44]. While there is evidence that religiosity may be protective against suicide in the broader population [45, 46], it has been found to be associated with greater recent suicidal ideation and attempts for sexual minority young adults [47].

In addition, while existing studies have largely focused on adolescents and young adults [2], most suicide deaths occur among those who are middle-aged [48], mirroring trends in the broader population [49]. Longitudinal research is also limited and again has focused predominantly on adolescents and young adults [50]. Experiences influencing mental health and suicide risk may change across the life course, and cohort effects have been observed among SGM populations. For example, in a national sample of sexual minority persons, those born in recent years (1990–97) were coming out earlier in life, perhaps reflecting broader societal shifts in acceptance [51]. However, this younger cohort did not report fewer distal stressors (e.g., discrimination) or proximal stressors (e.g., internalized stigma) compared to older cohorts (born between 1956–63 and 1974–81), and they also reported a greater prevalence of psychological distress and suicidal behaviors. Assessing a large sample of SGM adults across a wide age range, and following them longitudinally, is critical to understanding variation across the life course in terms of the development and progression of mental health conditions and suicidal behaviors.

Lastly, few studies have adopted an intersectional approach to understanding mental health disparities among SGM persons. The existing literature in this area has predominantly focused on white, cisgender samples, overlooking the unique stressors faced by individuals who experience multiple forces of marginalization [52]. Emerging research, however, has emphasized the ways in which intersecting forces of oppression and marginalization may shape mental health disparities among diverse SGM subpopulations in the US [53–55]. For instance, one longitudinal study conducted among cisgender Black, Latino, and multiracial sexual minority men found that the interaction between racial discrimination and internalized sexual orientation-related stigma contributed to greater levels of depression, anxiety, and alcohol use over the 12-month follow-up period [54]. There is also evidence that minority stress reflected in the experiences of individuals who vary in gender identity, gender expression, and sexual orientation may contribute to further mental health disparities among SGM subgroups. Indeed, several studies have suggested that individuals who identify as both sexual *and* gender minorities (e.g., gay transmasculine persons, bisexual gender non-conforming persons) have significantly worse mental health outcomes compared to those who identify only as sexual *or* gender minorities [56, 57].

In summary, there is a need for longitudinal investigations that characterize the complex and nuanced interrelationships between minority stressors, mental health conditions, and suicidal behaviors over time among heterogeneous rural SGM adults. This is necessary to create more targeted, acceptable, and impactful intervention content and strategies that mitigate stigma, promote mental health, and prevent suicidal behaviors. In response to these needs, the current study will enroll and follow a large and diverse group of SGM adults living in rural and small metropolitan areas in the US. The study has two specific aims: (1) determine whether classes of stigma, discrimination, and traumatic experiences vary across subgroups of rural SGM adults and whether these exposure classes are associated with an increased *prevalence* of depression, suicidal ideation, and suicide attempts; and (2) determine whether the classes identified in Aim 1 are associated with an increased *incidence* of depression, suicidal ideation, and suicide attempts among rural SGM adults.

## Methods/design

### Study design

This prospective longitudinal cohort study, “Rural Exploration and Approaches for LGBTQ + Mental Health (REALM),” will explore minority stress in relation to mental health conditions and suicidal behaviors over a 12-month period among rural SGM adults. We will use online processes to recruit and enroll a diverse sample of up to 2,500 SGM adults living in rural counties and small metropolitan areas in the US to complete an online baseline survey. All enrolled participants will subsequently be followed over a 12-month period, with repeated surveys at three-month intervals. The study has been approved by the Johns Hopkins Bloomberg School of Public Health Institutional Review Board (IRB No. 00022255).

This study builds upon prior collaborations between investigators at the Johns Hopkins Bloomberg School of Public Health and the Programs, Research, and Innovation in Sexual Minority (PRISM) Health team at Emory University’s School of Public Health (e.g., [58–62]). Our team of faculty, staff, and students work collaboratively across institutions, drawing upon research, practice, and lived experience in SGM stigma and mental health to inform our work. When constructing our team, we sought inclusion of individuals with diverse sexual orientations and gender identities, alongside interdisciplinary expertise in mental health, SGM health disparities, online survey research, epidemiology, qualitative research, and latent variable modeling.

In addition, all study activities are guided by a Community Advisory Board (CAB) consisting of up to 10 diverse members from the study’s target population. CAB members are recruited on an ongoing basis through email listservs from rural SGM-serving organizations, geo-targeted advertisements on social networking websites, participants of the current study, and – when necessary – participants of relevant studies external to the current study. Potentially interested candidates complete a brief application, with a subsequent internal review and interview process used for selection. Geographical location, gender identity, sexual orientation, and race/ethnicity are factors included in evaluation to ensure diversity and equitable representation of rural populations within the US. CAB members serve a 12-month term with possible contract renewal. CAB members are responsible for evaluating study design, recruitment strategies, recruitment materials, and survey items. The CAB meets quarterly, for a total of four meetings per study year. Compensation for CAB members includes $100 per hour for services and meetings.

### Participants

Study participants will include up to 2,500 adults aged 18 + residing in rural counties and small metropolitan areas (< 250,000 population) across the following groups: up to 1,000 cisgender sexual minority persons (up to *N* = 500 each cisgender women and cisgender men); and up to 1,500 gender minority persons (up to *N* = 500 persons who were assigned male at birth and identify as a woman, female, and/or transfeminine; up to *N* = 500 persons who were assigned female at birth and identify as a man, male, and/or transmasculine; and up to *N* = 500 persons who identify as some other gender, including non-binary, gender non-conforming, and/or agender regardless of sex assigned at birth). We define cisgender as those whose current gender identity aligns with conventional assumptions of their sex assigned at birth. Inclusion criteria across these groups is shown in Table 1. To explore differences by race/ethnicity, we aim to enroll racial/ethnic minority persons at a level that is, at minimum, representative of the national demographics of the rural US according to 2020 census estimates, and will target recruitment strategies to platforms that have greater racial and ethnic minority representation and limit inclusion criteria as necessary based on ongoing enrollment progress.

**Table 1 Tab1:** REALM cohort study inclusion criteria by participant type

Participant type	Inclusion criteria
Sexual minority persons	• At least 18 years old • Able to read English and/or Spanish • Willing to provide ≥ 2 means of contact and an emergency contact • Currently living in a rural county or small metropolitan area • Identifies gender as cisgender man or woman • Identifies sexuality as other than only heterosexual (specifically homosexual, including gay or lesbian; bisexual; pansexual; or queer)
Gender minority persons	• At least 18 years old • Able to read English and/or Spanish • Willing to provide ≥ 2 means of contact and an emergency contact • Currently living in a rural county or small metropolitan area • Identifies gender as something other than cisgender man or woman (specifically woman, female, transwoman, trans female or transfeminine when assigned male at birth; man, male, trans man, trans male, or transmasculine when assigned female at birth; or non-binary, gender nonconforming, or genderqueer)

### Sample size

We based our sample size calculations on limited previous studies capturing the prevalence of depression, suicidal ideation, and suicide attempts [1, 4, 7, 33, 63–71] – as well as distal minority stressors [34, 72, 73] – among SGM persons. For Aim 1, using conservative estimates, we expect a sample size of *N* = 500 in each SGM subgroup to provide a minimum of 98% power (normal approximation with continuity correction) to detect a 15% absolute difference in depression prevalence (estimated prevalence ratio of 1.6) between exposed and unexposed persons. We also expect this sample size to provide at minimum 98% power for a 15% absolute difference in both suicidal ideation and attempts. For the LCA, estimates of minimum required sample sizes in growth mixture models with 10 exposure measures ranged from 300 to 1,100 (in a six-class model with low class separation and 20% missing data) based on Monte Carlo simulations [74]. With an estimated 13 indicators of distal minority stressors, our total sample of 2,500 should therefore be adequate for estimating growth mixture models.

All participants will be followed for 12 months with a projected overall retention rate of 80% resulting in *N* = 400 participants in each SGM subgroup available for endline analyses. We will use the same retention procedures successfully implemented in a recent online prospective pilot study with gay men and other men who have sex with men that demonstrated retention rates of 98% at four months [75]. Though retention is not expected to vary by SGM subgroup, our Aim 2 power calculations account for expected variations in terms of the prevalence and incidence of depression and suicide attempts. Drawing on one general population study of depression incidence over a 24-month period [76], we have used a conservative estimate of average annual incidence of one-eighth of the estimated prevalence. We have also extrapolated from existing cross-sectional studies [7, 34, 66, 72, 73, 77, 78] to estimate that between 25–30% of participants will have additional exposures to distal minority stressors over the follow-up period.

Due to a lack of available studies, Aim 2 power calculations are based off 24-month rather than 12-month follow-up. We expect the projected sample size in each SGM subgroup followed through 24 months to provide a minimum of 78% power (normal approximation with continuity correction) to detect a 7% absolute difference in depression incidence (equivalent to an estimated incidence rate ratio of 4.5) between exposed and unexposed persons. Notably, these calculations are based on the sexual minority cisgender men subgroup of participants, who are predicted to have the lowest incidence of both depression and distal minority stressors. All other SGM subgroups are expected to have substantially higher power for depression incidence analyses: 84% for transgender men and transmasculine persons; 90% for sexual minority cisgender women; and 99% for transgender women and transfeminine persons.

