### Data analysis

For Aim 1, we will use latent class analysis (LCA) to explore how clusters of stigma, discrimination, and traumatic experiences (i.e., distal minority stressors) may be differentially associated with mental health-related outcomes among SGM persons at baseline. LCA is a person-centered analytic approach that allows for the identification of underlying classes of participants based on their responses to observed indicator variables [92]. Using the indicators described above to capture distal minority stressors, we will perform class enumeration by testing models with an increasing number of classes. The best fitting model will be selected using fit indices such as the Akaike Information Criteria, Bayesian Information Criteria, Vuong-Lo-Mendell-Rubin Likelihood Ratio Test, and entropy, and further evaluated based on theoretical interpretability [93]. All initial analyses will be conducted separately by the five SGM subgroups (sexual minority cisgender women, sexual minority cisgender men, transgender women and transfeminine persons, transgender men and transmasculine persons, and non-binary persons). Various modeling approaches will be examined to address potential effect modification by sexual orientation or gender identity within these five subgroups, and multigroup alignment optimization will be used to assess measurement invariance. If the latent classes are similar across subgroups, we will combine and repeat the effect modification and optimization analysis for gender minority versus cisgender participants. Finally, we will use the Bolck, Croon, and Hagenaars latent class regression approach to assess associations between class membership and prevalent depression, suicidal ideation, and suicide attempts [94]. In addition, age and racial/ethnic identities will be included as covariates, with possible interactions with latent class.

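### The Aim 1 power of at least 98% is for a two-group exposed/unexposed comparison and is not a minimum for the planned latent class analysis

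*Protocol article*

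**What the plan says.** The Sample size section bases Aim 1 on "a sample size of *N* = 500 in each SGM subgroup". It claims a "minimum of 98% power (normal approximation with continuity correction) to detect a 15% absolute difference in depression prevalence", with an "estimated prevalence ratio of 1.6) between exposed and unexposed persons". For the other two primary outcomes it claims "at minimum 98% power for a 15% absolute difference in both suicidal ideation and attempts", without base rates. A separate sentence there on latent class analysis cites simulated sample-size requirements of 300 to 1,100 and concludes that the total of 2,500 is adequate for estimating growth mixture models.

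The Data analysis section describes a different Aim 1 analysis. On the number of classes: "we will perform class enumeration by testing models with an increasing number of classes". On the level of analysis: "All initial analyses will be conducted separately by the five SGM subgroups". On the association with outcomes: "we will use the Bolck, Croon, and Hagenaars latent class regression approach to assess associations between class membership and prevalent depression". Age and race/ethnicity enter as covariates, with possible interactions with class. Subgroups are combined only if their classes turn out similar.

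**The concern.** A two-proportion formula treats each person as known to be exposed or unexposed and puts all 500 into one comparison. The planned analysis departs from this in two ways. With three or more classes, a comparison of two of them draws on only part of the 500. And because class membership is uncertain, the BCH correction raises the variance. Neither loss is in the printed figure, and nothing in the article maps exposed/unexposed onto the classes.

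The sentence on latent class analysis does not fill the gap. It concerns whether the model can be estimated, and it relies on 2,500 rather than 500.

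At stake is how the subgroup results are judged. Aim 1 asks whether exposure classes are associated with the outcomes. A reader who takes 98% as the floor in each subgroup will overrate what a subgroup analysis of 500 can detect.

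**Working it through.** **Inputs from the article (Sample size):** 500 per subgroup; 15-point difference; prevalence ratio 1.6. The last two give an unexposed prevalence of 0.15/0.6 = 25% and an exposed prevalence of 40%.

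**Assumed, because not stated:** two-sided 5%; exposed share; number and sizes of classes; classification accuracy, with errors spread evenly over the other classes. No multiplicity adjustment.

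**Step 1. The plan's own comparison.** Power = Φ{[|p1 − p0| − ½(1/n1 + 1/n0) − 1.96·SE0]/SE1}, where SE0 is the pooled and SE1 the unpooled standard error. At 250 vs 250: (0.15 − 0.004 − 1.96 × 0.0419)/0.0414 = 1.54, so power is 93.9%. This is the maximum over exposed shares; 30% exposed gives 89.5% and 20% gives 80.2%. The article's inputs therefore do not reproduce 98% at two-sided 5%. That is a separate point, and the one made here does not depend on it.

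**Step 2. Pairwise contrast, equal classes, perfect classification.** Same formula, 25% vs 40%, with 500/K persons in each class:

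| Classes K | Persons per class | Corrected difference | SE0 | SE1 | Power |
|---|---|---|---|---|---|
| 3 | 166.7 | 0.144 | 0.0513 | 0.0506 | 80% |
| 4 | 125 | 0.142 | 0.0592 | 0.0585 | 67% |
| 5 | 100 | 0.140 | 0.0662 | 0.0654 | 56% |
| 6 | 83.3 | 0.138 | 0.0726 | 0.0716 | 48% |

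Reaching 98% would need about 324 persons in each of the two classes compared.

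**Step 3. Classification error alone, two classes.** BCH weights are the inverse of the classification matrix. At 90% accuracy, with rows (0.9, 0.1) and (0.1, 0.9), they are 0.9/0.8 = 1.125 and −0.1/0.8 = −0.125. Power = Φ(0.15/SE − 1.96), using the asymptotic variance of the weighted difference and no continuity correction:

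- 50:50 split: SE rises from 0.0414 to 0.0519, and power falls from 95% to 82%.
- 27.5% in the exposed class: SE rises from 0.0476 to 0.0613, and power falls from 88% to 69%.

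The 27.5% is illustrative. It is the midpoint of the article's 25–30%, but that range describes additional exposures during follow-up, not exposure at baseline.

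**Step 4. Both losses together, 90% accuracy, extreme classes still 15 points apart.** Three equal classes give 71% and four equal classes give 60%.

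**Step 5. A graded pattern that favours the plan.** Here 15 points is roughly the average gap between the lowest class and the rest, so the extreme classes differ by more:

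- Classes of 50/30/20% with prevalences 25/35/50%. Average in the upper classes: (0.3 × 0.35 + 0.2 × 0.50)/0.5 = 41%, a gap of 16 points. Highest vs lowest (25 points): 99% with perfect classification and 95% at 90% accuracy.
- Classes of 40/30/20/10% with prevalences 25/35/45/55%. Average in the upper classes: (0.3 × 0.35 + 0.2 × 0.45 + 0.1 × 0.55)/0.6 = 41.7%, a gap of 16.7 points. Highest vs lowest (30 points): 97% and 88%. An overall test across the four classes gives 99% and 93%.

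**The case against.** The best case for the authors has four parts.

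- **The 98% is labelled.** The text ties it to exposed vs unexposed persons and treats latent class sample size in its own sentence. This stands in part. But the figure is introduced as the Aim 1 power, is called a minimum, and belongs to a comparison that the Aim 1 analysis does not contain.
- **No pairwise contrast is specified.** The article speaks only of associations with class membership, and an overall test uses all 500. This stands. The pairwise figures illustrate one possible contrast, not a test the plan has named.
- **Holding the extreme classes to 15 points is severe.** With graded prevalence their gap would be larger, and Step 5 shows that much of the loss is then recovered. This stands, and it is why a range is given.
- **Pooling restores power.** With all 2,500 and four equal classes, power stays above 98% even at 20% error. But the plan's pooling is into gender minority and cisgender groups, depends on the classes being similar, and comes after the subgroup analyses. The 98% is stated per subgroup of 500.

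One might also say that an article leaves power simulations to the full protocol. The point, however, is not an omission: two things the article does state do not match.

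Stronger readings are tempting but unsupported. A reader might infer that true power is about half the printed figure. That needs many classes or a small one (for example 50 vs 200 persons, 49% with perfect classification) and extreme classes held to 15 points, and the article fixes neither. Nor does it suggest that a null result would be presented as evidence of no association. This is also not an arithmetic error: it is a mismatch between power calculation and analysis.

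**Conclusion.** The mismatch holds on the text alone: the Aim 1 power is for a two-group comparison, and the Aim 1 analysis is a latent class regression within subgroups. The 98% therefore cannot be called a minimum for the planned analysis, for depression or for the two suicidality outcomes.

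The size of the shortfall is uncertain. It runs from little or none (graded prevalence with near-perfect classification), through 88–95% (graded, 90% accuracy), to 69–82% (two classes, 90% accuracy) and 80–48% (three to six equal classes, 15 points, perfect classification). Adding classification error lowers the last range further. All of these rest on assumed class numbers, sizes, accuracy and effect patterns, and on two-sided 5% without multiplicity adjustment. They show direction and range, not the study's actual power.

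**What to change.** Do one of two things.

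1. Restate the Aim 1 power for the class-outcome association by BCH within a subgroup of 500. Name the test (an overall class test or a specified contrast) and report power over a stated range of class numbers, class sizes, classification accuracy and effect patterns. A small simulation is enough.
2. Keep the 98%, but say that it applies only to a dichotomised observed exposure and does not cover the latent class analyses, and drop the word minimum.

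The first costs a short simulation and a rewritten paragraph; the second costs a sentence. Neither changes enrolment or conduct. The downside is a less favourable stated power.

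### The 98% power stated for Aim 1 depression does not follow from the other stated inputs; at two-sided 0.05 (assumed) those give at most about 94%

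*Protocol article*

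**What the plan says.** The Sample size section of the protocol article (under Methods/design) sets out the Aim 1 calculation in one sentence. The sample is stated as "we expect a sample size of *N* = 500 in each SGM subgroup". The method is "normal approximation with continuity correction". The target is a "15% absolute difference in depression prevalence (estimated prevalence ratio of 1.6) between exposed and unexposed persons". The resulting power is given as a "minimum of 98% power (normal approximation with continuity correction) to detect a 15% absolute difference in depression prevalence (estimated prevalence ratio of 1.6"), and the sentence says that conservative estimates were used.

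The article states no significance level, no sidedness and no exposed share for Aim 1. The only exposed share in the section comes with the Aim 2 assumptions, where the authors expect that "between 25–30% of participants will have additional exposures to distal minority stressors over the follow-up period".

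A further sentence covers the other two primary outcomes: "We also expect this sample size to provide at minimum 98% power for a 15% absolute difference in both suicidal ideation and attempts". It gives no ratio or base rate for either.

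**The concern.** An absolute difference and a ratio together determine both prevalences, so the depression statement can be checked from its own numbers. Apart from alpha, the only free input is how the 500 people divide into exposed and unexposed. If no division gives 98%, the printed figures cannot all be right.

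At stake is the only Aim 1 power figure for depression, a primary outcome, and it is claimed for every subgroup. A minimum of 98% implies a type II error of at most 2%. It also suggests ample room for a shortfall, when enrolment is capped at up to 500 per subgroup and the Discussion accepts that subgroup targets may not be met.

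**Working it through.** **Inputs**
- Difference d = 0.15 and ratio 1.6 (Sample size section). Unexposed prevalence p0 = 0.15 / (1.6 − 1) = 0.25; exposed prevalence p1 = 0.40.
- N = 500 per subgroup, exposed plus unexposed (same section).
- Normal approximation with continuity correction (same section).
- Alpha: not stated. Two-sided 0.05 assumed; one-sided 0.05 also tried.
- Exposed share for Aim 1: not stated. All shares from 5% to 95% scanned.

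**Formula**

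Power = Φ[(d − c − z·S0) / S1], where
- c = ½(1/n1 + 1/n0)
- S0 = √[p̄(1 − p̄)(1/n1 + 1/n0)], with p̄ the pooled prevalence
- S1 = √[p1(1 − p1)/n1 + p0(1 − p0)/n0]
- z = 1.96 (two-sided) or 1.645 (one-sided)

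**Attempt to reproduce 98%, even split (250/250)**
- p̄ = 0.325, S0 = 0.0419, S1 = 0.0414, c = 0.004.
- (0.15 − 0.004 − 1.96 × 0.0419) / 0.0414 = 1.545, so power is 93.9%.

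**Uneven split, 25% exposed (125/375)**
- p̄ = 0.2875, S0 = 0.0467, S1 = 0.0492, c = 0.0053.
- (0.15 − 0.0053 − 1.96 × 0.0467) / 0.0492 = 1.078, so power is 86.0%.

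**Across splits, two-sided 0.05 with correction**

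| Exposed share | Power |
|---|---|
| 25% | 86.0% |
| 30% | 89.5% |
| 40% | 93.0% |
| 50% (maximum) | 93.9% |

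Simulation gives 86.0%, 89.7% and 94.0% at 25%, 30% and 50% exposed.

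**Variants, each at its best split**

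| Variant | Maximum power |
|---|---|
| Two-sided, corrected, unpooled variance | 94.3% |
| Two-sided, no correction | 95.0% (95.3% unpooled) |
| Two-sided, corrected, most favourable rounding (difference near 15.5 points, ratio near 1.65) | 95.5% |
| One-sided, corrected | 96.9% (97.1% unpooled) |
| One-sided, no correction | 97.5% (97.7% unpooled) |
| One-sided, corrected, most favourable rounding | 97.8% |

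**Check against the Aim 2 figure**

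Aim 2 states 78% power for a 7-point difference at a rate ratio of 4.5. Then p0 = 0.07 / 3.5 = 0.02 and p1 = 0.09. With N = 400 and 25–30% exposed, the corrected two-sided formula gives 75.3–78.5%, in line with the stated 78%; one-sided gives 82.0–85.0%. This suggests that the authors used two-sided 0.05.

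**What would give 98%**

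At 25% vs 40%, two-sided and corrected, the total needed per subgroup is about 648 with an even split. With N = 500 and a 15-point difference, the unexposed prevalence must be at most about 14% with an even split (ratio about 2.1 or more). With 30% or 25% exposed it must be at most about 9% or 7% (ratio about 2.6 or 3.1).

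**The case against.** **Alpha is not stated.** With a one-sided 0.05 test, an even split and both inputs at the favourable edge of their rounding, power is 97.8%, which prints as 98%. That stands as arithmetic, and it is why the 94% ceiling must carry its two-sided assumption. It is a weak defence, however. It needs all of these choices at once for a figure described as a minimum on conservative estimates, and the Aim 2 figure points to two-sided testing. That comparison is itself only suggestive: it treats all 400 retained participants as at risk of incident depression.

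**A reader might take 500 as the size of each exposure group.** That gives 99.9%, not 98%, and it contradicts the statement that 500 is the size of each subgroup.

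**A reader might infer that the true power is 86–90%.** The article does not support that. The 25–30% share describes additional exposures during follow-up, an Aim 2 input. Aim 1 classes rest on baseline measures that include lifetime, childhood and past-year experiences, so the Aim 1 share could differ. Only the ceiling is independent of the split.

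**A reader might extend the error to suicidal ideation and attempts.** No ratio or base rate is given for these, and 98% is reachable at low prevalence: 5% vs 20% gives 99.0% at 25% exposed. Nothing in the article shows those figures to be wrong, and a condensed article may leave their inputs to the full protocol.

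**A reader might add that the latent class analysis can only have less power than this.** That does not follow. Data analysis allows subgroups to be combined if their classes are similar; at N = 1,000 the same contrast has over 99% power at 25–50% exposed. Contrasts between extreme classes may also exceed 15 points.

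**Conclusion.** Wrong as written, for Aim 1 depression only. The 98% power, 15-point difference, ratio of 1.6 and N = 500 do not reconcile under the stated method. Assuming two-sided 0.05, power is at most about 94%, so the stated minimum is at least 4 percentage points above the best case at the printed inputs. It remains about 2.5 points above with the most favourable rounding (95.5%). One-sided 0.05 at the printed inputs also falls short, at about 97%.

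The gap is wider if exposure is uneven: 12 points at 25% exposed and 8.5 at 30% exposed, both conditional on a share that the article does not give for Aim 1.

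This is a misstated figure and not an underpowered design. Power of roughly 86–94% across these illustrative splits is still above common targets of 80% to 90% at most of them and within that range at the rest. The check cannot show whether the power, the difference or the ratio was misprinted.

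**What to change.** Reconcile the depression sentence in one of two ways:
- If 25% vs 40% is what was intended, replace the minimum of 98% with at most about 94% (even split, two-sided 0.05) and give the value at the exposed share assumed for Aim 1.
- If the difference or ratio was misprinted, correct that input so that the stated power follows from it.

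In either case, show alpha and sidedness, the exposed share and both prevalences. The ideation and attempts sentence does not need to change on this ground.

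The cost is a text correction and, in the first case, a less favourable headline figure. Sample size, subgroup caps and analysis stay as they are.
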